#### Safety evaluation

2.13.3

Adverse events recorded in the patients’ diary will be analyzed as a multiply variable. The number and percentage of patients with AE will be calculated and compared using Chi-squared test.

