#### Withdrawal criteria

2.3.3

1.Violation of the inclusion criteria and clinical trial protocol or fulfillment of the exclusion criteria;2.Do not receive 10 consecutive treatment days or receipt of <20 rMS sessions;3.Serious adverse events;4.Loss to follow-up;5.Withdrawal of consent by the subject or a legal representative;6.Self-replacement of the treatment package that could affect the study results without permission from the investigator.

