### Adverse events observation

2.8

It could be that patients with epilepsy or headache, scalp discomfort, and tinnitus at stimulating are more likely related to rTMS. Regional skin numbness around the HT7 acupoint occur in patients is probably connected to rMS at HT7 acupoint. With the patients’ diary, all adverse events are to be recorded and measured during treatment and the follow-up period. Serious adverse events should be reported to the principal investigator immediately. All details will be documented, coil location and stimulus intensity adjustment (avoid the more sensitive orbitofrontal cortex, 100% RMT → 80% RMT), as well as appropriate medical care will be given at once. For the participants with severe CI during study, they would be administered with Eszopiclone tablets (3 mg Qn). However, if the subjects cannot tolerate the 80% RMT intensity and/or take Eszopiclone tablets more than twice a week, they will be considered as drop outs.

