### Quality control

2.14

The reasons of dropouts or withdrawals throughout the treatment and follow-up periods will be fully recorded. To ensure trial quality, the quality monitors will verify all the process details at regular intervals and check the authenticity of the data. Moreover, a 3rd party, scientific research department of Shaanxi Province Hospital of Traditional Chinese Medicine, will be invited to manage the data independently.

Since differences among physicians can cause bias, the evaluation of the rating scales in every time will be executed by one assigned physician who has been trained with the same criterion of evaluating. Two physicians responsible for treatment will receive special training about the study and manipulations including TMS use and locations of acupoints before recruitment. To record the attendance and compliance, we make record cards for patients which cover date of treatment, personal information, and their signatures after every treatment.

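### The safety comparison takes its events from the patient diary, so adverse events recorded by other routes are not guaranteed to enter the between-arm percentages

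*Protocol article*

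**What the plan says.** All references are to the protocol article.

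- **What is analysed (2.13.3 Safety evaluation).** "Adverse events recorded in the patients’ diary will be analyzed as a multiply variable". The next sentence gives the summary and the test: "The number and percentage of patients with AE will be calculated and compared using Chi-squared test".
- **How events are captured (2.8 Adverse events observation).** "With the patients’ diary, all adverse events are to be recorded and measured during treatment and the follow-up period". A second route follows for serious events: "Serious adverse events should be reported to the principal investigator immediately". The same section says that details, including changes of coil position and stimulus intensity, are documented.
- **Who leaves the trial.** The withdrawal criteria in 2.3.3 include "3.Serious adverse events;4.Loss to follow-up". Section 2.8 adds: "if the subjects cannot tolerate the 80% RMT intensity and/or take Eszopiclone tablets more than twice a week, they will be considered as drop outs".
- **Where reasons for leaving are kept.** Section 2.10 puts dropouts and their causes in the case report form, and 2.14 requires the reasons to be recorded in full. Section 2.2 has the ethics committee review any serious event.
- **Analysis sets (2.13).** Intention-to-treat and/or per-protocol, chosen in the light of missing data, with the two results compared for robustness. No set is assigned to safety.

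**The concern.** The article describes several places where a harm may be recorded but names one of them, the diary, as the source for the safety comparison. A statistician following 2.13.3 literally would build the table from diary entries. An event seen by the operator, reported as serious, or given as the cause of a dropout would count only if the patient had also written it down.

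Two further features make this matter more. Harm is itself a reason to leave the trial under 2.3.3 and 2.8, and the and/or wording in 2.13 permits a per-protocol set from which those participants would be absent. Also, the arms are not equally exposed to the intolerance rule, so any loss by that route could distort the comparison as well as the level.

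The potential risks of stimulating the head are part of the article's argument for trying the acupoint instead (Introduction and Discussion). The event percentages are the only planned between-arm summary of harm.

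**Working it through.** The document states no adverse-event rate, safety sample size or safety power, so there is no figure to reproduce. The check is a comparison of the text, followed by arithmetic on assumed counts.

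**Step 1. Follow each type of event from record to table.**

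| Event | Where it is recorded | Named in 2.13.3? |
|---|---|---|
| Written down by the patient | Diary (2.8) | Yes |
| Serious event | Report to principal investigator (2.8); ethics review (2.2) | No |
| Change of intensity or coil position | Documented (2.8) | No |
| Harm that caused withdrawal or dropout | Case report form (2.10); reasons recorded (2.14) | No |

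The gap is between record and analysis. It is not a gap in recording.

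**Step 2. Where the intolerance rule can apply.** The HT7 arm is stimulated at 25% RMT (2.7.1.1) and the r-DLPFC arm at 100% RMT (2.7.2.1). A step down from 100% to 80% RMT therefore has meaning in the r-DLPFC arm. It also has meaning in the waiting-list arm once that arm is treated like the positive control from day 11 (2.7.3). The other limb of the rule (eszopiclone more than twice a week) and the serious-event criterion apply to any arm.

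**Step 3. Size per patient.** Section 2.5 gives n = 15 per arm. If k patients have an event recorded only outside the diary and stay in the denominator, the shortfall is k/n:

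- k = 1: 1/15 = 6.7 points
- k = 2: 2/15 = 13.3 points
- k = 3: 3/15 = 20.0 points

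Section 2.1 gives a total of 54 instead of 45. At 54/3 = 18 per arm, one patient is 1/18 = 5.6 points.

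**Step 4. Worked illustration (assumed counts).** In an arm of 15, 5 patients have an event and 2 of these are withdrawn for it.

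- All sources, everyone counted: 5/15 = 33.3%
- Diary only, the 2 events recorded elsewhere: 3/15 = 20.0%
- The 2 patients dropped by a per-protocol set: 3/13 = 23.1%
- The 2 events also in the diary, everyone kept: 5/15 = 33.3%, so no loss

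With 1 to 3 such patients and 2 to 4 others having an event, the diary-only shortfall is 6.7 to 20.0 points. If those patients are dropped from both counts, it runs from 5/15 − 4/14 = 4.8 points to 5/15 − 2/12 = 16.7 points.

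**Step 5. Direction.** Losing events lowers the percentage, but a per-protocol set can also raise it. If 2 patients without any event drop out, for example for eszopiclone use, the rate becomes 5/13 = 38.5%. The net direction is not fixed by the document.

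**The case against.** The strongest reply is that nothing here need be lost. Section 2.8 requires all events to be recorded through treatment and follow-up. Serious events reach the principal investigator at once and the ethics committee reviews them. Intensity changes are documented, and dropout causes go to the case report form. Section 2.13.3 names the diary without excluding other sources, and its second sentence counts patients with an event without repeating the restriction. Withdrawal does not erase an entry already in the diary. No sentence says that the diary stops at withdrawal or that safety uses a per-protocol denominator. A safety set and a serious-event listing are commonly left to a full protocol or analysis plan.

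Most of this stands, and it rules out several stronger readings that a reader might infer:

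- *The worst and clinician-observed harms are the ones most likely to be lost.* Not supported, because they have their own recording routes.
- *The percentages are biased down, mainly in the r-DLPFC arm, because only that arm can trigger the intolerance rule.* Not supported. The waiting list can trigger it from day 11, the loss may be zero, and the net direction is open.
- *The treatment card shows that operator-observed events are not captured.* The card is described thus: "we make record cards for patients which cover date of treatment, personal information, and their signatures after every treatment". Its stated purpose is attendance and compliance, so the absence of an event line on it proves nothing about safety recording.
- *Comparative tolerability is a central objective.* The stated primary objectives are short-term efficacy and mechanism. The risks of cranial stimulation appear as motivation only.

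What the reply does not remove is that 2.13.3 states a source for the analysed events, and no sentence joins the other records to it. This is a stated rule rather than a detail left out.

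**Conclusion.** The point holds in a limited form. As written, the safety comparison rests on diary entries. Serious-event reports, documented intensity changes and dropout causes are recorded but are not brought into it, and the and/or choice of analysis set leaves the safety denominator open. Harms recorded elsewhere are therefore not guaranteed to enter the between-arm percentages.

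The size per patient is firm: 6.7 points at 15 per arm. The number of patients affected is unknown and may be zero. The illustrated shortfalls depend wholly on the assumed counts. This is an inexpensive improvement to a small pilot's safety table, and no evidence of biased results.

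**What to change.** Replace the source and denominator in 2.13.3 with wording to this effect:

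> *Adverse events from all recorded sources (patient diary, serious-event reports, documented intensity changes, and causes of withdrawal or dropout) will be counted once per patient and event. All participants will be included according to the treatment received, regardless of later withdrawal or dropout; the per-protocol set will not be used for safety. For the waiting-list group, untreated days 1–10 and the stimulated period from day 11 will be reported separately.*

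The split for the waiting list is needed because, from day 11, events in that arm arise under the same stimulation as the positive control and cannot serve as an untreated comparison.

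The change uses records that the article already requires and alters no dose, withdrawal rule or rescue rule. Its cost is some reconciliation of diary, reports and case report form, so that one event is not counted twice, and possibly a higher reported adverse-event rate. Collection after withdrawal and the layout of the treatment card can be left to the full protocol.

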### Study design

2.1

This is a single-center, randomized, positive-controlled, noninferiority clinical pilot trial. A total of 54 participants will be randomized into 3 groups at a ratio of 1:1:1. Participants in the treatment group will be treated with rMS at HT7 acupoint. Participants in the control group will be treated with rTMS at r-DLPFC or waiting treatment.

The whole study period is 35 days, including 5-day baseline observation, 10-day treatment, and 20-days follow-up. Subjects will be evaluated with scales for clinical efficacy before and the 10th day of treatment, 30th day of follow-up, and monitored by rMS/rTMS for therapeutic mechanism before and the 10th day of treatment, 30th day of follow-up (Fig. 1).

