### Study group

2.5

Forty-five participants who meet the criteria with informed consents will be selected. The subjects will be randomly divided into 3 groups in a 1:1:1 ratio, namely the experimental group, positive-control group and waiting list control group, 15 cases in each group.

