### Estimation of sample size

2.11

This study is just a pilot study, which designed for efficacy evaluation and mechanism investigation of targeted therapy preliminarily before and after treatment as well as follow-up period. We will plan to enroll a total of 45 participants in this study.

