### Statistical analysis

2.13

Data analysis will be based on intention-to-treat analysis and/or per-protocol analysis principle in the light of data missingness. We will also evaluate the group effect by comparing the analysis results between the above 2 data sets to evaluate robustness of our analytical results.

All data will be analyzed using SPSS23.0 (v23.0; SPSS Inc, Chicago, IL) by 3rd-party statistician. A *P* value <.05 will be considered as significant. Descriptive statistics will be performed with mean, standard deviation, maximum, minimum, and so on by groups and time.

Baseline characteristics of patients will be summarized by groups and compared with Chi-squared for categorical variables, and analysis of variance (ANOVA) (normal distributions) or Kruskal–Wallis test (non-normal distributions) for the continuous variables. Primary and secondary outcomes according to the measurement times are applicable to univariate repetitive measurement deviation analysis or ANOVA or Kruskal–Wallis test. If there is a violation of distribution assumption, appropriate transformation will be used.

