Our protocol is just a pilot study with several limits including the small sample size, open-blinding, and short period of observation time. However, we try our best to attempt to minimize the biases that may influence study results. Finally we intend to demonstrate the hypothesis that rMS at HT7 acupoint as an alternative may be validated for CI.

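### The adverse-event comparison rests on a Chi-squared test at P<.05 with about 15 patients per arm, which is too weak to inform comparative safety; differences should be estimated with intervals

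*Protocol article*

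**What the plan says.** Section 2.13.3 of the protocol article (Safety evaluation) sets out the comparison: "The number and percentage of patients with AE will be calculated and compared using Chi-squared test". Section 2.13 gives the general threshold: a P "value <.05 will be considered as significant". No interval, margin or exact test is named for adverse events, and the article does not say whether the test is across three arms or pairwise, or whether it is continuity-corrected.

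On size, section 2.5 plans "15 cases in each group" and section 2.11 agrees: "We will plan to enroll a total of 45 participants in this study". Section 2.1 differs: "A total of 54 participants will be randomized into 3 groups at a ratio of 1:1:1", which is 18 per arm. Section 2.11 gives no power calculation and explains the size by the study's purpose: "This study is just a pilot study, which designed for efficacy evaluation and mechanism investigation of targeted therapy preliminarily".

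Two other sections bear on the comparison. Section 2.8 records adverse events through both treatment and follow-up. Section 2.7.3 moves the waiting-list arm to the positive-control treatment from day 11.

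**The concern.** Safety is part of the case for stimulating HT7 instead of the head. The Introduction looks for a method without side effects, and the Discussion sets the HT7 approach against the risks of stimulating the head. A reader will therefore want to know how adverse events compare between arms.

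The only between-group output planned beyond counts and percentages is a test of no difference. At this size the test will usually be non-significant even if one arm is clearly worse. The Chi-squared approximation is also poor when few events are expected, and the article names no fallback for sparse tables, although section 2.13 does give alternatives for non-normal continuous data. At stake is a safety paragraph that reports no significant difference and does not show how large a difference the data still allow.

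**Working it through.** **Inputs.** From the article: 15 per arm (sections 2.5 and 2.11) or 54/3 = 18 (section 2.1); Chi-squared test (2.13.3); threshold .05 (2.13). Assumed, because the article gives none: AE rates, a 20-point excess, and no continuity correction.

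**Plan's own figure.** 3 × 15 = 45 agrees with section 2.11. No power or AE rate is stated, so nothing further can be reproduced.

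**Expected counts.** With overall AE rate p, the expected count per arm is n × p. It is below 5 when p < 5/15 = 33%, or p < 5/18 = 28% with 18 per arm.

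**What the test needs to reach P<.05.** For a versus b events in two arms of n, X² = 2n(a(n−b) − b(n−a))² / [n²(a+b)(2n−a−b)].
- 3/15 v 0/15: 30 × 45² / (225 × 3 × 27) = 3.33, P = .07, not significant.
- 4/15 v 0/15: 30 × 60² / (225 × 4 × 26) = 4.62, P = .03, significant.
- Against 2/15, the other arm needs at least 7/15.

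**Hand check of one miss rate.** For true rates of 0% v 20%, the pairwise test misses when the second arm has 3 events or fewer: 0.035 + 0.132 + 0.231 + 0.250 = 0.648.

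**Miss probabilities.** All possible tables were enumerated, and the binomial probabilities of those not significant under the uncorrected test were summed.

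| Assumed rates | Pairwise, n=15 | Three-arm, one arm raised, n=15 | Three-arm, one arm raised, n=18 |
|---|---|---|---|
| 5% v 25% | 68.8% | 65.7% | 57.6% |
| 10% v 30% | 72.2% | 73.0% | 66.5% |
| 20% v 40% | 76.7% | 76.9% | 73.3% |

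**Sensitivity at 15 per arm.**
- The lowest miss rate found is 40% (three-arm, 0% v 20% v 0%). Pairwise 40% v 60% gives 82%.
- If two of the three arms are raised, as could happen once the waiting list is treated, the three-arm test misses 76% to 80% at comparator rates of 5% to 20%.
- For the three pairs in the table, a Yates correction gives misses of 91.0%, 89.3% and 89.5%. Fisher's exact test gives 83.3%, 85.1% and 88.8%.
- The true size of the uncorrected three-arm test is 0.5% at a common AE rate of 2%, and 2.4% at 5%.

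**What an interval would show.** Take 5/15 v 2/15 as an example. X² = 30 × (5×13 − 2×10)² / (225 × 7 × 23) = 1.68, P = .195. The difference is 20 points. The Wilson limits are 15.2% to 58.3% and 3.7% to 37.9%, so the Newcombe limits are:
- lower: 0.200 − √[(0.333−0.152)² + (0.379−0.133)²] = −0.105
- upper: 0.200 + √[(0.583−0.333)² + (0.133−0.037)²] = +0.467

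The test reports no significant difference, while the interval runs from −11 to +47 points. With no events in 15 patients, the one-sided 95% upper bound is 1 − 0.05^(1/15) = 18.1%.

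**The case against.** The strongest reply is that the article claims nothing false here. It describes a pilot and lists the small sample among its limits. Any AE comparison at 15 per arm is weak, and rewording the analysis does not add power. Detection of serious harm does not rest on this test: section 2.8 requires diary recording and immediate reporting of serious events, and section 2.2 gives the ethics committee prompt review and power to suspend. Intervals and exact tests are often left to an analysis plan that is not shown.

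Much of this stands. The low power is a consequence of the pilot size, and the remedy is a better report of what the data can say. The reply does not remove the point, because section 2.13.3 names a specific test, and that named choice is ill suited to the planned size. A pilot is also where estimation is more useful than testing.

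A reader might infer that the trial will declare the arms comparably safe whenever P>.05. The document does not support that. It states no safety hypothesis and no rule for a non-significant result, and its one interpretive sentence (section 2.13.1) concerns a significant group effect on the insomnia severity index and the resting motor threshold. The Discussion's aim that "rMS at HT7 acupoint as an alternative may be validated for CI" does not mention adverse events. The misreading is a risk, not a planned step.

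**Conclusion.** The point holds as a weakness in the chosen analysis. A Chi-squared test at .05 is the only between-group AE comparison specified. Under assumed comparator rates of 5% to 20%, the uncorrected test misses a 20-point excess in one arm about 66% to 77% of the time with 15 per arm, and about 58% to 73% with 18 per arm (three-arm). These ranges depend on the assumed rates and the test variant: the full spread found at 15 per arm runs from 40% for the most favourable three-arm case to more than 90% with a continuity correction. Under nearly all these assumptions a non-significant result is the likelier outcome, and it would say little about comparative safety.

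**What to change.** In section 2.13.3, make estimation the safety analysis:
- Report the number and percentage of patients with at least one AE per arm, with exact (Clopper-Pearson) 95% intervals.
- Report HT7 minus r-DLPFC as a risk difference with a 95% Newcombe interval.
- Report each active arm minus waiting list in the same way, for days 1 to 10 only. From day 11 the waiting list receives the positive-control treatment (section 2.7.3), so a later contrast would no longer be with an untreated arm.
- For any AE type with no events in an arm, give the one-sided 95% upper bound (18% for 0/15).
- Treat any P value as descriptive. Fisher's exact test is valid for sparse tables but has even less power than the uncorrected Chi-squared test, so it does not replace the intervals.
- State that P>.05 will not be taken as evidence of equal safety.

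The totals of 45 and 54 should be reconciled so that the denominators are clear. The change needs no new patients or data. Its cost is a less favourable-looking safety statement, because the wide intervals will be visible.

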### Quality control

2.14

The reasons of dropouts or withdrawals throughout the treatment and follow-up periods will be fully recorded. To ensure trial quality, the quality monitors will verify all the process details at regular intervals and check the authenticity of the data. Moreover, a 3rd party, scientific research department of Shaanxi Province Hospital of Traditional Chinese Medicine, will be invited to manage the data independently.

Since differences among physicians can cause bias, the evaluation of the rating scales in every time will be executed by one assigned physician who has been trained with the same criterion of evaluating. Two physicians responsible for treatment will receive special training about the study and manipulations including TMS use and locations of acupoints before recruitment. To record the attendance and compliance, we make record cards for patients which cover date of treatment, personal information, and their signatures after every treatment.

## Discussion

3

The CI is a persistent insomnia disease, which the course of the disease is >3 months and frequency more than 3 times/wk.^[8]^ The onset of CI is affected by many factors involving age, gender, medical history, stress events, personality traits, inheritance, mental disorders, physical diseases, and so on.^[25]^ Refer to the diagnostic criteria of CI, CI patients who are long-term subjected to insomnia problem, will bring direct or indirect harm to the society. Therefore, according to patients symptoms combined with rating scale, we hope to obtain high quality study data from this preliminary clinical trial that could provide reliable basis to future multicenter research.

The rTMS at r-DLPFC which is chosen as a positive controlled therapy for CI in this study has been recommend by experts consensus.^[12]^ As a noninvasive stimulation technique, rTMS can test changes in motor evoked potential, brain electrical activity, cerebral blood flow, metabolism, and brain functional status from the changes in neural activity.^[27]^ Besides, DLPFC plays an important role in our cognition, decision, and memorization, which is always as an effective stimulating target for the treatment of insomnia and depression, especially low-frequency (1 Hz) rTMS at DLPFC.^[12]^ However, rTMS on the static head directly might be limited with some potential risks like scalp tingling and burning, hearing impairment, even seizure, especially for the ones with metal implants in skull or body.^[28]^ Moreover, it is inconvenient for insomnia patients to receive continuing care in daily life with rTMS at DLPFC. For this, rMS at acupoint on CI may be a promising alternative therapy. Acupoints have been widely used and received in clinical practice in China.^[29]^ Patients in China are usually familiar with acupuncture, and expect to receive acupuncture treatments. Thus, since acupuncture is often regarded as an invasive operation,^[30]^ it is difficult to replicate its manipulations in clinic and design a nonpenetrating sham acupuncture in trial.^[31]^ Hence, aim to improve subjects compliance and achieve acupoint effect, we choose rMS at HT7 acupoint in the experimental group in a high-quality randomized controlled trial. Although studies have showed the efficacy of rTMS for CI,^[32,33]^ it is still lack rMS at acupoint randomized controlled trial, as well as the relevant mechanism research.

Our protocol is just a pilot study with several limits including the small sample size, open-blinding, and short period of observation time. However, we try our best to attempt to minimize the biases that may influence study results. Finally we intend to demonstrate the hypothesis that rMS at HT7 acupoint as an alternative may be validated for CI.
